## Abstract

**Background:**

Chronic obstructive pulmonary disease (COPD) is a significant health problem worldwide. This randomised controlled trial aims at testing a new approach that involves a registered nurse working in partnership with patients, general practitioners (GPs) and other health professionals to provide care to patients according to the evidence-based clinical practice guidelines. The aim is to determine the impact of this partnership on the quality of care and patient outcomes.

**Methods:**

A cluster randomised control trial design was chosen for this study. Randomisation occurred at practice level. GPs practising in South Western Sydney, Australia and their COPD patients were recruited for the study.

The intervention was implemented by nurses specifically recruited and trained for this study. Nurses, working in partnership with GPs, developed care plans for patients based on the Australian COPDX guidelines. The aim was to optimise patient management, improve function, prevent deterioration and enhance patient knowledge and skills. Control group patients received 'usual' care from their GPs.

Data collection includes patient demographic profiles and their co-morbidities. Spirometry is being performed to assess patients' COPD status and CO analyser to validate their smoking status. Patients' quality of life and overall health status are being measured by St George's Respiratory Questionnaire and SF-12 respectively. Other patient measures being recorded include health service use, immunisation status, and knowledge of COPD. Qualitative methods will be used to explore participants' satisfaction with the intervention and their opinion about the value of the partnership.

**Analysis:**

Analysis will be by intention to treat. Intra-cluster (practice) correlation coefficients will be determined and published for all primary outcome variables to assist future research. The effect of the intervention on outcomes measured on a continuous scale will be estimated and tested using mixed model analysis of variance in which time and treatment group will be fixed effects and GP practice and subject nested within practice will be random effects. The effect of the intervention on the dichotomous variables (such as smoking status, patient knowledge) will be analysed using generalised estimating equations with a logistic link and a model structure that is analogous to that described above.

**Trial registration:**

ACTRN012606000304538

## Background

### Significance of COPD

Chronic obstructive pulmonary disease (COPD) is a leading cause of disability, hospital admission and premature mortality in men and women [1]. According to WHO estimates, there are 210 million people worldwide who have COPD [2]. In 2005, there were 3 million deaths from COPD globally and the projection is that the mortality from COPD will increase by 30% over the next 10 years unless urgent actions are taken to combat it [2].

The prevalence of COPD (GOLD stage 2 or higher, that is post-bronchodilator FEV_1_/FVC ratio < 0.7 and FEV_1 _< 80% predicted) in a representative sample of people aged 40 years and over living in south-east Sydney in 2006 was 10.8%. This was in the mid-range of estimates for centres in 12 countries that participated in the first round of the BOLD international comparative study [3]. In recent years there has been a decline in death rates from COPD, but it still remains the fifth leading cause of death for males (40.6 deaths/100,000 population) and the seventh leading cause of death for women (19.5 deaths/100,00 population) in Australia [4].

In addition to the significant social and economic burden of deaths caused by COPD, the condition also poses a significant burden on the Australian health care system through hospitalisation of COPD patients with complications. In 2001–02, COPD led to 51,621 admissions Australia-wide, with an average stay of 7.5 days [3]. Nationwide, costs of COPD including hospitalisation, together with related community medical care, pharmaceutical services and indirect costs such as lost productivity are estimated to be in the range of 820 – 900 million Australian dollars annually [5].

### Evidence-based management

Guidelines for diagnosis and management of COPD are now available. In Australia the COPDX guidelines are commonly used which detail recommendations for preventing or slowing disease progression and optimising function for COPD patients [6]. The key recommendations include:

• Smoking cessation

• Pulmonary rehabilitation

• Influenza vaccination

• Optimising the use of inhaled bronchodilators & corticosteroids

• Patient education.

Despite the publication of the COPDX guidelines there is a low level of awareness about the existence of such guidelines among GPs in Australia [7]. To reduce the impact of COPD in Australia initiatives to encourage GP uptake of guideline recommendation are warranted.

### Role of General Practice in COPD management

General practice is well placed to provide early intervention and management of COPD patients. In Australia, general practice is the most common point of contact in the health system as 87% of people visit their GPs at least once a year [8]. COPD accounts for 0.6% of all problems managed in general practice [9]. While improved care in the community has the potential to substantially improve outcomes, research to date suggests that GPs experience difficulties providing care for patients with chronic illness under the current model of care which is largely encounter based and does not involve non-GP health providers [10]. There is a need for more structured systems to implement chronic illness care such as a multidisciplinary care plan. The use of care plans has become a recommendation for the management of people with chronic illnesses such as diabetes and asthma [11-13]. Similar to these patients, COPD patients often have complex needs and the COPDX guidelines[6] recommend the use of multidisciplinary care plans. However, research suggests that GPs need more external support to develop and implement multidisciplinary care plans for these patients [14-16].

### Role of nurses in care of COPD

A review of the roles of specialised nurses in care of patients with diabetes or COPD found evidence that they improved patient self care, quality of life and satisfaction [17]. A Cochrane review revealed that a nurse outreach program involving nurse home visits to COPD patients providing support and education, monitoring health status and providing liaison with physicians resulted in improved quality of life and reduced mortality [18]. A New Zealand study, that involved practice nurses and GPs implementing a care plan with advice from a respiratory nurse and specialist physician, resulted in reduced hospital admissions and reduced hospital bed days and there were significant improvements in spirometry [19].

### Lesson learnt from a previous study

A randomised controlled trial (RCT) [20] conducted in 1998–99 which evaluated the effect of a brief, nurse-led intervention at 1 week and 4 weeks interval after discharge from hospital on clinical outcomes in patients with COPD. The aim was to evaluate the efficacy of limited community based care provided by nurses to COPD patients. Results from this study demonstrated limited success. There were some improvements in activity and knowledge scores of patients in the intervention group and they were more satisfied with their care, but there was no impact on rates of emergency department presentation and hospital readmission. We subsequently attributed the failure of the intervention to three key reasons 1) GPs were not sufficiently involved in the patient care (evident by the fact that only 31% of the GPs recalled having received patient related information (care plan) from the nurses), 2) there was no formal partnership between GPs and nurses streamlining patient care, and 3) the unavailability of universally accepted guidelines for management of COPD such as, COPDX.

### Aim of the study

The aim of this study is to test a new approach to improving the care of patients with COPD managed in general practice. The intervention involves a registered nurse with specific training working in partnership with the patient, GPs and other health professionals to provide evidence-based care according to the Australian COPDX guidelines. The research aims to determine the impact of this partnership on the quality of care and health outcomes for patients with COPD at six and 12 months follow-up.

These are the hypotheses being tested:

1. That in patients with COPD, the intervention improves disease-related quality of life and overall health including patient health status, lung function and health service use.

2. That the intervention improves the quality of care provided to patients with COPD and that this will impact on knowledge, immunisation compliance, smoking cessation and satisfaction with care.

### Research Plan

A cluster randomised control trial design has been chosen for this study. As GPs find it difficult to selectively offer interventions to their patients, the cluster design was implemented to avoid contamination between intervention and control groups. Randomisation occurred at practice level and an adjustment to the sample size estimates allowed for clustering.

### Recruitment

#### General Practitioner/practice recruitment

GPs were recruited from a list of 256 GPs practising in South Western Sydney (SWS). The list includes GPs who have previously participated in research and/or attended local continuing medical education (CME) activities and also includes the chief investigators' personal contacts. Letters of invitation were sent to these GPs with a copy of the GP information statement. Within one to two weeks of the initial invitation telephone contacts were made with the GPs by one of the chief investigators to explain the study, check their eligibility, answer their questions about the study and formally invite them to participate. The GPs expressing interest were visited by the chief investigator at their practices. At the practice visit the details of involvement were explained and written consent was obtained. Inclusion criteria for GPs were: practising in SWS, use of an electronic prescribing system, and having seen COPD patients in the past 12 months. The aim was to recruit at least 40 GPs.

#### Patient recruitment

Participating GPs were asked to search their electronic prescription records and identify patients who had been prescribed medications for COPD. These were defined as inhaled beta 2-agonists, inhaled corticosteroids, ipratropium bromide, tiotropium, oral theophylline and oral corticosteroids. Patients' were eligible if they were aged between 40 and 80 years, prescribed one or more of the above medications, have seen the GP in the previous 12 months, and had a clinical diagnosis of either COPD, emphysema or chronic bronchitis. Patients who lived outside SWS, did not speak English, or had significant cognitive impairment were excluded from the study.

Letters were sent to the eligible patients inviting them to take part in the study. The letters included a patient information sheet and a consent form. Those who consented to take part returned the form to the research team. The project officer from the research team then contacted these patients and organised a home visit (or at the GP surgery if preferred by patient) to collect the baseline data as detailed below.

Two two-weekly reminders were sent to the non-responding patients. The aim was to recruit 400 patients from 40 GPs (an average 10 patients per GP).

### Randomisation

Practices were allocated to intervention and control groups according to a computer generated list comprising 11 randomly permuted blocks of size four. A system of sealed envelopes was used; a sealed envelope for each block contained four sequentially labelled sealed envelopes. A researcher not involved with the study and blind to the identity of the GPs undertook the randomisation. Once baseline data collection had been completed for the patients visiting a number of practices the practices were stratified according to whether they had recruited more than ten patients or less than ten patients and then allocated to a block of four. The envelope was opened and the individual practices were allocated to intervention or control depending on the contents of the four sequentially labelled envelopes. The research nurses and GPs were informed of the intervention allocation by the study administrator. The data collection staff remained blind to the allocation to prevent bias in data collection.

### Intervention

The intervention was implemented by nurses specifically recruited for this study. Nurses worked in partnership with GPs to implement the intervention. Nurses had been specifically trained to enable them to successfully implement the intervention. The training program for the nurses included attendance at a two-day workshop where the following topics were presented by expert clinicians: patho-physiology of COPD, assessment of COPD, spirometry, smoking cessation, management of COPD according to COPDX guidelines, role of pulmonary rehabilitation in the management of COPD, and the management of exacerbations.

### Intervention process

The intervention nurses worked with GPs, patients and other care providers as shown in Figure 1. Patients in the intervention group received two home visits and five telephone contacts from the nurse and a minimum of two consultations with their GP over a six-month period. The nurse and GP met face to face on two occasions and further consultation between the nurse and GP took place by telephone monthly or more frequently as needed to discuss progress and problems of the patients involved.

**Figure 1 F1:**
[figure not shown]

### Care plan content

The care plan is based on the recommendations of the COPDX evidence-based guidelines [6]. The plan aimed to optimise management, improve function, prevent deterioration and enhance patient knowledge and skills. The care plan was individualised to meet the needs of the patients and contained relevant components of the following:

1. Smoking cessation

2. Immunisation status

3. Pulmonary rehabilitation

4. Medication review

5. Nutrition

6. Psychosocial issues

7. Patient education

8. Co-morbidities and complications of COPD

#### Control Group

Patients in the control group received 'usual' care from their GPs. They were provided with a copy of the COPDX guidelines. 'Usual' care is defined as processes normally followed by the GP and the patient regarding review, pharmacological therapy and management of COPD.

#### Outcome evaluation

Quantitative outcomes were measured using instruments with demonstrated validity and reliability. A portable carbon monoxide (CO) analyser was used to validate participants' self-report of smoking status. These measures were implemented by two members of the research team who were blinded to the patients' group allocation. Data collectors received training in spirometry and use of the CO analyser.

Outcomes were measured at three points in time – at recruitment (baseline), 6 months and at 12 months after randomisation. [Table 1 shows outcomes measures being collected] These were measured at the participant's residence or at the GP practices as preferred by the patient.

**Table 1 T1:** Schedule of data collection

	**At identification**	**At recruitment**	**6-months**	**12-months**
Age, gender, language spoken	X	X		
Demographic information		X		
Index of Comorbidity		X		
Number medication classes		X	X*	X
St George's Resp Ques		X	X	X
Spirometry		X	X	X
Immunisation status		X	X	X
Patient knowledge of COPD		X	X	X
Patient satisfaction with care		X	X	X
Smoking status: self-report		X	X	X
CO analyser		X	X	X
Health status (SF12)		X	X	X
Health service use		X	X	X
Value of partnership		X	X	X
Role and value of care plan				X

* respiratory medications only

Qualitative data about the value of the nurse-GP partnership and the role of the care plan will be collected from the intervention group by structured interviews at the conclusion of the project following collection of the 12 month quantitative outcomes.

#### Baseline measures

Patient demographic details such as age, gender, employment status, education, and country of birth are recorded at baseline. Information regarding their COPD and smoking history are also collected at baseline. Spirometry is performed to assess their COPD status and CO analyser is used to validate their smoking status. Co-morbidity is assessed using two measures: the Geriatric Index of Comorbidity [21] and the number of classes of medication used.

### Quantitative outcome measures

**Patient quality of life: (hypothesis 1) **was assessed using the St George's Respiratory Questionnaire (SGRQ) [22] at baseline and 12 month follow up. The SGRQ is a self-administered instrument designed specifically for respiratory disease. It is a 50-item instrument from which are calculated a total score and three component scores: symptoms (distress caused by respiratory symptoms), activity (physical activities thai are limited by breathlessness) and impacts (social and psychological effects of the disease). The SGRQ is scored from zero to 100 where zero indicates best quality of life and 100 worst. A change in score of four is considered to be clinically significant [22,23].

**Lung function: (hypothesis 1) **Spirometric function was measured before and 10 minutes after the administration of 200 μg sulbutamol via large volume spacer, according to standard methods. Forced expiratory volume in one second (FEV_1_) and forced vital capacity (FVC) were recorded.

***Patient health status*: (hypothesis 1) **was measured using the SF-12 [24], a generic measure of health impairment. The SF-12 gives two scores, the mental components scale and the physical component scale, which both have a mean of 50 and a standard deviation of 10.

***Health service use*: (hypothesis 1) **the number and type of general practice, specialist, community health, and hospital services used during the 12 months study period were recorded using a patient checklist of services.

***Immunisation status*: (hypothesis 2) **details of immunisation status for influenza and pneumococcal infection were collected by patient report.

***Patient knowledge *(hypothesis 2) **of the steps that can be taken to reduce the progression of COPD was assessed using the same measure as in the previous trial [20]. Patients were asked to name up to three things that they could do to prevent progression of their lung disease.

***Patient satisfaction*: (hypothesis 2) **with the overall management will be measured at 12 months using the questionnaire used in our previous study [20]. In addition, focus groups will also be conducted with a sub-set of patients in the intervention group to explore the issues even further.

***Smoking status and cessation*: (hypothesis 2) **the smoking status of patients at baseline was established by recording the number of cigarettes smoked and the length of time before the first cigarette in the morning (a measure of addiction) [25]. Attendance at a smoking cessation program and quit rates were recorded.

### Qualitative process measures

#### Value of the nurse and GP partnership

Structured interviews with the respiratory nurses and the GPs will examine satisfaction with the program and perceptions of the value of working together. Structured interviews with patients will explore the effects and value of the nurse input into COPD care. The software package NVivo^® ^will be used to facilitate coding, and exploration of the data.

#### Statistical Analysis

Data are stored in an Access database and will be exported for analysis to SPSS. Analysis will be by intention to treat. Intra-cluster (practice) correlation coefficients will be determined and published for all primary outcome variables to assist future research. Potential confounders will be compared between groups to confirm that the randomisation has provided the appropriate balance.

The effect of the intervention on outcomes measured on a continuous scale (such as SGRQ score) will be estimated and tested using mixed model analysis of variance in which time and treatment group will be fixed effects and GP practice and subject nested within practice will be random effects. The effect of the intervention on the dichotomous variables (such as smoking status, patient knowledge) will be analysed using generalised estimating equations with a logistic link and a model structure that is analogous to that described above.

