#### Sample size calculations

The primary outcome variable will be 'between group' differences in post-test (12-months) is mean SGRQ scores. Data from our previous study [20] demonstrates that the between subject standard deviation in SGRQ scores is 13. The recommended minimum detectable difference to use for sample size calculations with SGRQ is 4.0 [22,23]. We have based our calculations on a intra-cluster correlation coefficient of 0.01 and a resultant design effect of 1.09 for a cluster size of 10 [26]. With this design effect the study has a > 80% power to detect a difference of 4 or greater in SGRQ. This requires at least 20 practices in each group and at least 10 patients per practice and that is at least 200 subjects in each group, (calculations in PASS software).

We estimated that the prevalence of COPD among general practice patients would be about 4.0%, slightly higher than population estimates [3]. Assuming that there are 1,500 adult patients registered with each GP then we would expect that there would be 60 patients with COPD. If a third of these patients would be eligible and consent to participate in the study, thus we will recruit 20 patients per practice. Taking a conservative approach and assuming 10 patients consent per practice, then to achieve 400 patients we will need to recruit 40 GP practices. As previously stated there are currently 785 GPs in 467 practices in SWS. Based on our previous experience of EPC evaluation [14] where 71% of the GPs contacted took part in the research we expect to be able to recruit the numbers of GPs and practices needed for this efficacy trial.

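### The stated SGRQ model names neither baseline SGRQ as a covariate, nor the randomisation stratum, nor the term that gives the 12-month difference made primary

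*Protocol article*

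**What the plan says.** The Statistical Analysis section, and the Analysis paragraph of the Abstract, give one model for continuous outcomes. In it "time and treatment group will be fixed effects"; GP practice, and subject nested within practice, are random. No other term is listed. On baseline variables the section adds only that "Potential confounders will be compared between groups to confirm that the randomisation has provided the appropriate balance".

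Under Sample size calculations, "The primary outcome variable will be 'between group' differences in post-test (12-months) is mean SGRQ scores". The trial is sized on the unreduced between-subject SD.

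Under Randomisation, allocation follows baseline data collection, and "the practices were stratified according to whether they had recruited more than ten patients or less than ten patients". A practice with exactly ten patients falls in neither group, and ten is the cluster size used for planning.

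The SGRQ schedule is given in two ways. The Quantitative outcome measures section has it at baseline and 12 months. Table 1 also marks 6 months.

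**The concern.** Baseline SGRQ and practice size are both known before allocation and cost nothing more to use. With about 40 randomised practices, a chance difference between arms in baseline SGRQ is quite possible. An analysis of follow-up values alone carries that difference forward, in proportion to the baseline-to-12-month correlation, and gives up precision.

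The listed terms also do not show which coefficient estimates the primary quantity. A group main effect equals the 12-month difference only if 12 months is the sole time in the model or the effect is constant over the times included. If baseline is one of those times, the effect cannot be constant, because no treatment has yet been given.

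Comparing confounders to confirm balance does not settle either matter. Chance imbalance is compatible with a sound randomisation, and the article gives no rule for what follows if imbalance is seen.

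**Working it through.** **Inputs from Sample size calculations.** The difference is 4 ("The recommended minimum detectable difference to use for sample size calculations with SGRQ is 4.0"). The SD is 13 ("the between subject standard deviation in SGRQ scores is 13"). The clustering inputs are "a intra-cluster correlation coefficient of 0.01 and a resultant design effect of 1.09 for a cluster size of 10". Each arm has 20 practices and 200 patients.

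**Assumed.** Two-sided alpha is 0.05, since none is stated. The baseline-to-12-month SGRQ correlation r is not in the article; 0.3 to 0.7 is used.

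**1. The plan's own figure.**
- Design effect = 1 + 9 × 0.01 = 1.09.
- SE = 13 × √(2 × 1.09/200) = 1.357, and 4/1.357 = 2.947.
- Power is 83.8% (normal) or 81.9% (t with 40 − 2 = 38 df). The stated power above 80% is reproduced.
- For 80% power, 166 × 1.09 = 181 patients per arm are needed, below the planned 200.

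**2. Follow-up values only, with and without baseline as covariate.** Split the variance of 169 into a practice part, 0.01 × 169 = 1.69, and a patient part, 167.31. Baseline adjustment multiplies the patient part by 1 − r², and the practice part is cautiously left unchanged:

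SE = √(2 × [167.31 × (1 − r²)/200 + 1.69/20])

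| r | SE | Power (t, 38 df) |
|---|---|---|
| unadjusted | 1.357 | 82% |
| 0.3 | 1.301 | 85% |
| 0.5 | 1.193 | 90% |
| 0.6 | 1.113 | 94% |
| 0.7 | 1.011 | 97% |

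**3. Baseline as a time level, effect read as a change contrast.** For a like-for-like comparison, the whole variance is now scaled and the normal approximation used, so the covariate column is slightly higher than in step 2. The multiplier is 2(1 − r) for change and 1 − r² for the covariate.

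| r | Change contrast | Baseline covariate |
|---|---|---|
| 0.3 | 70.2% | 87.1% |
| 0.5 | 83.8% | 92.6% |
| 0.7 | 96.8% | 98.5% |

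Since 1 − r² = (1 − r)(1 + r) and 1 + r ≤ 2, the covariate analysis is at least as precise at every r. Its advantage is about 9 percentage points at r = 0.5 and 2 at r = 0.7.

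**4. Baseline as a time level, only the listed main effects fitted.** With times 0 and 12 months, the group term averages the two differences: (0 + 4)/2 = 2 points. The variance multiplier is (1 + r)/2.
- r = 0.5: SE = 13 × √(0.75 × 2 × 1.09/200) = 1.175, power about 40%.
- r = 0.7: SE = 13 × √(0.85 × 2 × 1.09/200) = 1.251, power about 36%.

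**5. Upper bound on the gain from the stratum.** If practice size explained all between-practice variance, the factor 1.09 would fall by 10 × 0.01 to 0.99. Then SE = 13 × √(2 × 0.99/200) = 1.293, and power rises from 83.8% to about 87.1% (normal). The realistic gain is smaller.

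**The case against.** The strongest reply is that a fixed time effect with a random subject effect is a repeated-measures model. Baseline is one of the general measurement times. On the schedule in Quantitative outcome measures, time has two levels for SGRQ only if baseline is one of them. A reader might infer that the plan makes no use of baseline SGRQ; the article does not establish that, because baseline may be a repeated response. Nor does it say that the 12-month difference will be unadjusted. This stands, and it narrows the gain to that in step 3. It does not complete the specification: the term that would carry the 12-month effect is still unnamed, and step 4 shows what the listed terms alone would estimate.

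Three other inferences go too far.
- *The balance comparison replaces adjustment.* The article says neither this nor that tests will be used or covariates chosen from the result. What can be criticised is the stated purpose of confirming balance.
- *The trial is underpowered.* Its own inputs give more than 80% without adjustment.
- *Omitting the stratum costs much precision or makes the standard error too small.* At ICC 0.01 the possible gain is small, and omitting a stratification factor generally makes inference conservative.

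Finally, this is a condensed article, and a fuller plan may list covariates. That silence alone would be no finding. But the article does set out a model with named terms, and those terms neither reflect the stratified allocation nor yield the declared primary quantity.

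**Conclusion.** The point holds as one of incomplete specification and avoidable loss of precision. The named terms leave the role of baseline SGRQ and the 12-month contrast undefined, and they omit the stratification factor.

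The size depends on which model is meant:
- **Follow-up values only:** about 82% power, against 85% to 97% with baseline adjustment for r from 0.3 to 0.7.
- **Change contrast:** the covariate analysis is still at least as precise, with 93% against 84% at r = 0.5 (normal approximation).
- **Main effects only at 0 and 12 months:** a 4-point effect would be estimated as about 2.

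These figures rest on the assumed r, a two-sided alpha of 0.05, and the article's SD, ICC and full planned numbers with no dropout. The case for the stratum is mainly agreement between analysis and randomisation. The gap at exactly ten patients is a plain defect in the text, though its effect cannot be quantified from the article.

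**What to change.** - Define the primary estimate as the treatment contrast in SGRQ at 12 months. Obtain it either from a model with follow-up SGRQ as response and baseline SGRQ as covariate, or from a repeated-measures model with time-by-group in which the arms share a common baseline mean. Baseline must not be both response and covariate. If more than one follow-up time is modelled, include time-by-group in the first option too.
- Add the practice-size stratum as a fixed effect, and state in which stratum practices with exactly ten patients were actually placed.
- Present the baseline comparison as a descriptive table and say that it does not determine the covariates.
- Reconcile the two SGRQ schedules so that the levels of time are clear.

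This costs wording and a few model terms, with no new data and no change to sample size. By the article's Time plan, 12-month follow-up is still to come, so the change can be fixed before primary outcome data exist.

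### The published mixed model lists time and treatment group but no group-by-time term, baseline covariate or 12-month contrast, so as written it does not estimate the primary 12-month SGRQ difference

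*Protocol article*

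**What the plan says.** All references are to the protocol article.

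- **Target.** Under Sample size calculations: "The primary outcome variable will be 'between group' differences in post-test (12-months) is mean SGRQ scores". The stated power of more than 80% for a 4-point difference refers to this quantity.
- **Model.** Under Statistical Analysis, and again in the Abstract, the effect on continuous outcomes is to be estimated and tested in a "mixed model analysis of variance in which time and treatment group will be fixed effects", where "GP practice and subject nested within practice will be random effects". Neither place names an interaction, a baseline covariate or a contrast at a particular visit. Dichotomous outcomes get GEE with an analogous structure.
- **Visits.** Under Outcome evaluation: "Outcomes were measured at three points in time – at recruitment (baseline), 6 months and at 12 months after randomisation"; Table 1 marks SGRQ at all three. Quantitative outcome measures instead gives the questionnaire ("SGRQ) [22] at baseline and 12 month follow up"), with no 6-month visit.
- **Order of events.** Under Randomisation, practices were allocated "Once baseline data collection had been completed for the patients visiting a number of practices", so baseline SGRQ precedes allocation.

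**The concern.** A repeated-measures model with time and group as its fixed effects and no product term forces the group difference to be the same at every visit. Its one treatment coefficient is then a visit-averaged difference. The primary outcome is the difference at a single visit, 12 months. The two coincide only if the effect is constant over every visit in the model. It cannot be constant if one visit is a pre-allocation baseline, where the expected difference is zero.

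At stake are the main estimate and its test. A diluted coefficient would be judged against the 4-point clinical threshold that the article uses both for interpretation and for sample size, so a real 4-point benefit could be reported as falling short of it. The GEE models inherit whatever structure the continuous model has.

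**Working it through.** **Inputs from Sample size calculations:** SD 13, difference 4, ICC 0.01, 20 practices of 10 patients per group (200 per group).

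**Assumed, because the article does not give them:** two-sided alpha 0.05; within-subject correlation ρ of SGRQ between visits (given practice) 0.5 to 0.8; no loss to follow-up; the effect at 6 months, varied below. Power uses the noncentral t with 40 − 2 = 38 degrees of freedom.

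**Step 1. Reproduce the plan's figure.** Design effect = 1 + (10 − 1) × 0.01 = 1.09, as stated. For a 12-month comparison, SE = √(2 × 13² × 1.09 / 200) = 1.357 and 4 / 1.357 = 2.95. Power is 82% with 38 df (84% by normal approximation). The stated figure of more than 80% is sound for the 12-month difference.

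**Step 2. What the listed model estimates.** With balanced data, the group coefficient is the difference between groups in subject means over the T visits modelled:

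- Expected value = (sum of the visit-specific group differences) / T.
- Practice variance τ = 0.01 × 169 = 1.69; remaining variance σ² = 169 − 1.69 = 167.31.
- SE = √{2 × [σ² × (1 + (T − 1)ρ) / (T × 200) + τ / 20]}.

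For T = 2 the SE is 1.193 at ρ = 0.5 and 1.294 at ρ = 0.8. For T = 3 it is 1.133 and 1.272.

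**Step 3. Results for a true 4-point effect at 12 months** (power at ρ = 0.5, then ρ = 0.8).

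| Visits in the model | Group difference at each visit | Expected coefficient | Power |
|---|---|---|---|
| 12 months only (plan's calculation) | 4 | 4 | 82% |
| Baseline, 12 | 0, 4 | 4/2 = 2.0 | 37% to 33% |
| Baseline, 6, 12 | 0, 4, 4 | 8/3 = 2.67 | 63% to 53% |
| Baseline, 6, 12 | 0, 2, 4 | 6/3 = 2.0 | 41% to 34% |
| Baseline, 6, 12 | 0, 0, 4 | 4/3 = 1.33 | 21% to 18% |
| 6, 12 | 4, 4 | 8/2 = 4.0 | 90% to 85% |
| 6, 12 | 2, 4 | 6/2 = 3.0 | 69% to 62% |

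The expected coefficients do not depend on ρ; only the power figures do. A small simulation of the patient-level model (60 runs, ρ = 0.7, subject intercept only) gave mean group coefficients of about 2.2 with two visits and 2.7 with three. The 12-month interaction term averaged 3.9 to 4.0.

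**Step 4. Is baseline a level of time?** The article does not say so outright. On the two-visit schedule under Quantitative outcome measures it must be, because a time effect and a subject random effect need at least two visits and baseline is one of only two. On Table 1's three-visit schedule it is the natural reading, because baseline is given no other role in the model.

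**The case against.** The strongest reply is that the sentence sorts the design factors into fixed and random and need not be a full list of model terms. It does not say that no interaction will be fitted. The article is condensed, the full protocol and any SAP are not shown, and the sample size section does name the 12-month target, so the two sections could be read together as a 12-month contrast from a repeated-measures model.

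Part of this stands. A reader might infer that the trial will certainly fit main effects alone and report a diluted estimate. The documents do not show that: the absence of an interaction is read from a list, and baseline as a level of time is stated nowhere and forced only on the two-visit schedule. What remains is more than missing detail. The article specifies the model twice, down to its random effects, says it will both estimate and test the intervention effect, and the terms it lists do not yield the stated primary outcome.

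A second reply is that only 6 and 12 months may be modelled. That is possible on Table 1's schedule and removes the dilution. The coefficient is still a 6- and 12-month average, and matches the target only if the effect is the same at both.

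A third concerns size. A reader might infer that most of the planned power is lost. In the three-visit case with 4 points at both follow-ups it is not: 53–63% remains of 82%. The 18–21% case supposes no effect at 6 months, which is hard to square with an intervention delivered over a six-month period.

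**Conclusion.** Wrong as written. The model as published does not estimate the 12-month between-group SGRQ difference that the article defines as primary and uses for power. The sample size arithmetic itself is correct.

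The size depends on which visits enter:

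- **Baseline included:** the expected estimate of a 4-point effect is half its value with two visits. With three visits it is at most two-thirds, provided the 6-month effect does not exceed 4. Power is then roughly 33–37% or, in that most favourable three-visit case, 53–63%, against about 82%.
- **Follow-up visits only:** there is no loss if the effect is constant. If it grows from 2 to 4 points, the expected estimate is 3.0 and power 62–69%.

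The power figures rest on the assumed alpha, correlation, 6-month effect and absence of loss. The mismatch between model and primary outcome rests on none of these.

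**What to change.** In the analysis section, before the data are analysed:

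1. Fit SGRQ at 6 and 12 months with group, time and group-by-time, and baseline SGRQ as a covariate. Alternatively, keep baseline as an outcome and constrain the groups to a common baseline mean. Keep practice and subject within practice as random effects. If SGRQ proves to have been collected only at baseline and 12 months, the covariate form reduces to a 12-month model with practice as the random effect.
2. Name the 12-month between-group contrast from that model as the primary estimate and test, with 6 months as a secondary contrast.
3. Carry the same structure into the GEE models for dichotomous outcomes.
4. Reconcile the SGRQ visits: Outcome evaluation and Table 1 give three, Quantitative outcome measures gives two.

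The cost is a few sentences and no new data. Under the same assumptions a baseline-adjusted 12-month contrast has power of about 90–99%, so the sample size need not change on this account.
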